## Abstract

As the treatment of nonspecific chronic cough with conventional medications that treat cough according to the cause is limited, *Maekmundong-tang* (comprising Liriopis seu Ophiopogonis Tuber, Pinelliae Tuber, Oryzae Semen, Zizyphi Fructus, Ginseng Radix, and Glycyrrhizae Radix et Rhizoma) has been used empirically in the clinical setting of East Asian traditional medicine. This study is the first to explore the feasibility, preliminary effect, safety, and cost-effectiveness of *Maekmundong-tang* for nonspecific chronic cough. This study protocol is that of a double-blind, randomized, active-controlled, parallel-group clinical trial for comparing *Maekmundong-tang* with *Saengmaek-san* (comprising Liriopis seu Ophiopogonis Tuber, Ginseng Radix, and Schisandrae Fructus), a Korean national health insurance-covered herbal medicine for cough. A total of 30 nonspecific chronic cough patients will participate and receive the assigned herbal medicine for 6 weeks, and clinical parameters will be assessed at weeks 0 (baseline), 3 (midterm assessment), 6 (primary endpoint), 9, and 24 (follow-up). Study feasibility outcomes, including recruitment, adherence, and completion rates, will be assessed. Preliminary effects on cough severity, frequency, and quality of life will be evaluated using outcome measures, such as the Cough Symptom Score, Cough Visual Analog Scale, and the Leicester Cough Questionnaire. Adverse events and laboratory tests will be monitored for safety evaluation, and exploratory economic evaluations will be conducted. The results will provide evidence of *Maekmundong-tang* in the treatment of nonspecific chronic cough.

## 1. Introduction

The prevalence of cough is about 2.3–18% of the adult population worldwide, and among them, the prevalence of chronic cough, lasting more than 8 weeks in adults, is reported to be about 10–38% [1,2]. Common causes of chronic cough include upper airway cough syndrome, asthma including cough variant asthma, and gastroesophageal reflux disease [2]. In most cases, the cause of chronic cough can be identified and treated if appropriate examination and treatment are performed according to the guidelines and protocols presented in various clinical practice guidelines [3,4]. However, in the case of some chronic coughs, it is difficult to identify the cause and the cough cannot be treated even with these tests and treatments. Recent opinions suggest that these cases should be approached as a different clinical disease [5].

Nonspecific chronic cough is defined as cases where no specific findings are observed in history taking, physical examination, chest X-ray, and pulmonary function test in patients with chronic cough [6]. In conventional medicine, oral antihistamines, inhaled corticosteroids, leukotriene receptor antagonists, and proton pump inhibitors have been suggested empirically for the treatment of nonspecific chronic cough according to symptoms [6]. However, concerns about the side effects during long-term use and the lack of evidence have raised questions about their effectiveness [6,7]. As a result, many patients are seeking complementary and integrative medicine, including herbal medicine, to treat chronic cough [8,9].

*Maekmundong-tang* (*Maimendong-tang* in Chinese, *Bakumondo-to* in Japanese) is an herbal medicine that has long been used in clinical settings for the treatment of nonspecific chronic cough. It consists of Liriopis seu Ophiopogonis tuber, Pinelliae tuber, Oryzae semen, Zizyphi fructus, Ginseng Radix, and Glycyrrhizae Radix et Rhizoma. It was first introduced in Essential Prescriptions from the Golden Cabinet (Jingui Yaolüe), which explains treating cough and discomfort in the throat with qi reflux. While the effects of *Maekmundong-tang* on coughs related to chronic airway diseases and cough hypersensitivity accompanied by chronic cough have been reported by various experimental and clinical studies [10,11,12,13], the evidence is still uncertain. In addition, the effect of *Maekmundong-tang* on chronic cough has not been reported since the time nonspecific chronic cough has been clearly defined. Therefore, in this study, we will confirm the feasibility of large-scale clinical trials based on recruitment, adherence, and completion rates by administering *Maekmundong-tang* to patients with nonspecific chronic cough. In addition, *Saengmaek-san* (*Shengmai-san* in Chinese, *Shomyaku-san* in Japanese; comprising Liriopis seu Ophiopogonis Tuber, Ginseng Radix, and Schisandrae Fructus), the health insurance covered herbal medicine for cough treatment, was set as a control intervention to explore the possibility of *Maekmundong-tang*’s health insurance coverage through a cost-effectiveness analysis.

## 2. Methods

### 2.1. Study Design and Recruitment

A single-center, double-blind, randomized, active-controlled, parallel-group clinical trial will be conducted at the Daejeon Korean Medicine Hospital of Daejeon University in the Republic of Korea from February 2023 to December 2024. Only those individuals who voluntarily sign the written informed consent form to participate in the clinical trial after receiving a comprehensive explanation from the licensed Korean medicine doctors about the trial will be tested at the screening visit. Participants who satisfy the eligibility criteria will visit the hospital within 7 days to 3 weeks after the screening visit and will be randomly allocated to either the *Maekmundong-tang* group or the *Saengmaek-san* group in a 1:1 ratio. All groups will take investigational products for 6 weeks, and participants will visit the hospital every 3 weeks to undergo clinical evaluation. After taking the drug, a revisit will be performed 3 weeks later (week 9) to evaluate the effect and safety, and a telephone follow-up will be conducted at week 24 to conduct the economic evaluation (Table 1 and Figure 1). In summary, this study has a total of 6 visits (including 1 phone survey), and it will take approximately 6 months. To recruit participants, recruitment documents will be posted on hospital bulletin boards, websites, and applications. Additionally, subway, bus, and newspaper advertisements will also be implemented if recruitment is delayed. All trial processes will be conducted in accordance with the Declaration of Helsinki and Good Clinical Practice Guidelines. In particular, *Maekmundong-tang* has cough as an indication. In the Republic of Korea, a clinical trial is exempted from investigational new drug application if it targets a drug already approved by the Korean Ministry of Food and Drug Safety and is conducted within the scope of the indication permitted [14]. Therefore, pre-clinical data such as toxicity data are unnecessary for this type of clinical trial.

### 2.2. Inclusion Criteria

(1) adults between the ages of 19 and 75

(2) those who have a cough lasting more than 8 weeks

(3) those who have signed an institutional review board (IRB)-approved written informed consent form to participate in this study voluntarily

### 2.3. Exclusion Criteria

(1) those who have been diagnosed with other causes of chronic coughs, such as chronic respiratory diseases (chronic obstructive pulmonary disease, bronchial asthma, bronchiectasis, interstitial lung disease, pulmonary tuberculosis, etc.), gastroesophageal reflux disease, chronic sinusitis, and allergic rhinitis within the last 2 years

(2) those who have the following symptoms that can be presumed to cause cough: wheezing, chest tightness, dyspnea, runny nose, nasal congestion, sneezing, postnasal drip, abnormal findings in the ear canal, heartburn, reflux, fever, and hemoptysis

(3) those with abnormal findings on a chest X-ray that may cause cough 

(4) those with abnormal findings in the pulmonary function tests

(5) those with wheezing, rales, postnasal drip, or cobblestone throat during the physical examination

(6) those who have been diagnosed with an acute respiratory disease within the last 4 weeks

(7) those who are current smokers, quit smoking within 3 months, or have a history of excessive smoking in the past 30 pack years or more

(8) those who are taking angiotensin-converting enzyme (ACE) inhibitors or dipeptidyl peptidase-4 (DPP-4) inhibitors or have taken them within the last 4 weeks

(9) those who have taken antitussives, expectorants, steroids, anti-leukotrienes, anticholinergics, long-acting beta 2 agonists (LABA), oral antihistamines, or any herbal medicine within the past 2 weeks

(10) those who have been diagnosed with a malignant tumor within the last 5 years

(11) those with severe liver or renal disease (aspartate aminotransferase (AST) or alanine aminotransferase (ALT) levels ≥ 3 times the upper limit of normal or creatinine levels ≥ 2 times the upper limit of normal) 

(12) those with a history of serious alcohol or drug abuse 

(13) women of childbearing age who are pregnant or lactating or who do not agree to use an effective method of contraception during the trial period

(14) those with genetic problems such as galactose intolerance, Lapp lactase deficiency, or glucose-galactose malabsorption

(15) those with known hypersensitivity to the investigational products 

(16) those who had taken other investigational products within 3 months 

(17) those who have not recorded a cough diary for at least 7 days immediately prior to the baseline visit

(18) those with average daytime cough symptom score (CSS) < 2 points and night-time CSS < 1 point according to the cough diary recorded for the 7 days immediately before the baseline visit

(19) those who are judged to be inappropriate for participating in this study by the investigators

### 2.4. Randomization and Blinding

The randomization sequence will be generated by block randomization method (mixing block sizes of two and four) without stratification. The allocation ratio for each group is 1:1. The randomization sequence will be generated using the statistical program SAS^®^ Version 9.4 (SAS Institute Inc., Cary, NC, USA) by a medical statistician, independent of the interventions and evaluations in this clinical trial. Participants who meet all the eligibility criteria will be allocated from the minimum available number to each group. 

In this clinical trial, all participants, investigators, and outcome assessors are blinded. Each participant’s group information according to the randomization order will be put in an opaque sealed envelope. It will not be disclosed until the end of the clinical trial, except when it is unavoidable to view group information due to the occurrence of a serious adverse event.

### 2.5. Interventions

All investigational drugs were manufactured by Kyungbang New Pharmaceutical Co., Ltd. (Incheon, Republic of Korea) in compliance with the 2021 Korean Good Manufacturing Practice guidelines. All participants will be allocated to the *Maekmundong-tang* or *Saengmaek-san* groups. Each 2.5-g serving of *Maekmundong-tang* granule (Yunpye-tang extract granule, Maekmundong-tang; product code: 200005808) comprises grayish-brown granules that consist of 1250 mg *Maekmundong-tang* dry extract, 625 mg corn starch, and 625 mg lactose hydrate. The raw materials and composition of *Maekmundong-tang* dry extract 1250 mg are as follows: Liriopis seu Ophiopogonis Tuber 3.33 g, Pinelliae Tuber 1.67 g, Oryzae Semen 3.33 g, Zizyphi Fructus 1.00 g, Ginseng Radix 0.67 g, and Glycyrrhizae Radix et Rhizoma 0.67 g. Similarly, each 1.41 g serving of *Saengmaek-san* powder (Kyungbang *Saengmaek-san*, mixed single extract; product code: 200005617), the active control drug, is a brown powder that consists of 0.75 g Liriopis seu Ophiopogonis Tuber extract, 0.30 g Ginseng Radix extract, and 0.36 g Schisandrae Fructus extract. The investigator will instruct all participants to orally consume 1 pack of the formulation 3 times a day, before or between meals, for 6 weeks. Each of the herbal medicine was produced simultaneously in one batch and therefore has the same batch number. Their expiration date is 36 months from the date of manufacture. They should be stored in airtight containers at room temperature (1–30 °C). 

To improve the compliance of the participants of the clinical trial, the investigator will check the participant’s investigational product intake during the administration period and record details of compliance in the case report form (CRF); participants with less than 70% medication compliance at Week 6 will be dropped out.

The investigator will provide a multidimensional behavioral therapy (speech pathology therapy) guideline, which is a non-pharmacological treatment for cough, to all participants and educate the participants about this therapy [15]. This includes the creation of awareness that repetitive coughing is not beneficial and that coughing can be controlled by oneself through the suppression of the cough reflex that is induced by stimuli by swallowing saliva or water, or breathing with pursed lips when about to cough [15]. In addition, the education includes the vocal hygiene method, which ensures the supply of moisture to reduce laryngeal irritation, and psychological education counseling therapy, which helps patients recognize that chronic cough is difficult to treat and thereby set realistic treatment goals [15].

During the clinical trial period, new intake of any prescription drugs and over-the-counter medicines, except for investigational products and drugs allowed at screening visit, should be avoided. In particular, the trial should be discontinued if the following medications or treatments are required due to the participants’ circumstances or clinical condition: ACE inhibitor, DPP-4 inhibitor, antitussive, expectorants, steroid, antileukotrienes, anticholinergic, LABA, oral antihistamines, traditional Korean treatment (e.g., herbal medicine, acupuncture, etc.) to improve chronic cough, and other drugs or treatments that, in the investigator’s judgment, may affect the results of the clinical trial. 

At any time during the trial, the participants can voluntarily withdraw their participation for reasons such as dissatisfaction with the treatment effect. If participants are no longer able to participate in the trial due to adverse events or intercurrent diseases during the trial or have received the contraindicated drugs, which may affect the research outcomes, the participants will be dropped from the study at the investigators’ discretion. 

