### 2.6. Outcome Measures

#### 2.6.1. Study Feasibility Outcomes

As the primary purpose of this clinical trial is to evaluate the feasibility of a large-scale herbal-medicine clinical trial for nonspecific chronic cough, the following eight feasibility outcomes will be assessed in consultation with specialists in respiratory medicine by referring to the Consolidated Standards of Reporting Trials statement for feasibility trials and similar studies [16,17,18]: (1) Recruitment rate of the clinical trial: the percentage of the number of enrolled participants to the total number of participants screened for eligibility during the clinical trial period; (2) Total participant recruitment period of the clinical trial: the time elapsed between the first and last participant’s screening visit (to estimate the recruitment period of the future confirmatory clinical trial); (3) The average number of enrolled participants per month during the clinical trial recruitment period; (4) Average compliance of participants with investigational products: the average percentage of individual participants’ actual use of investigational drugs during the clinical trial period as opposed to the intended use of those drugs; (5) Clinical trial adherence rate: the percentage of participants who take 70% or more of all investigational products compared to the total number of participants enrolled in the clinical trial; (6) Average cough diary record compliance of participants: the average percentage of the number of days in the cough diary actually logged by individual participants during the clinical trial period compared to the intended number of days; (7) Completion rate of clinical trial: the percentage of participants who complete the trial without dropout, including follow-up periods of 9 and 24 weeks, respectively, to the total number of enrolled participants in the clinical trial; and (8) Dropout rate of clinical trial: the percentage of participants who drop out before the end of the clinical trial to the total number of enrolled participants.

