#### 2.6.2. Effectiveness Outcomes

The primary effectiveness outcome is the CSS score at Week 6. The CSS is a scale for the subjective assessment of cough severity and frequency that is reported by the patient during the daytime (08:00–20:00) and nighttime (20:00–08:00), and each subdomain of the scale is assigned 6 points, from 0 to 5. The total score is calculated as the sum of the daytime and nighttime scores (0–10 points) [19]. The validity and replicability of the Korean version of CSS have been verified [20]. Until Week 9, participants will be instructed to self-evaluate the CSS twice a day and record the score in a cough diary. During the telephonic follow-up survey (Week 24), participants will be asked to respond on their cough symptoms during the daytime and nighttime of the previous day. For statistical analysis, the average value (total, daytime, and nighttime scores) of the CSS since the previous visit that has been recorded in the cough diary and will be collected at each visit (excluding the baseline visit) will be used, and the average value of the previous 7 days will be used for determining the status at the baseline visit. The investigator will educate the participants on how to write a cough diary at every visit and attempt to minimize omissions in records. If less than 70% of the cough diary distributed at each visit has been completed, the participant will be dropped out.

The secondary outcome measures include the CSS (at weeks 3, 9, and 24), cough visual analog scale (VAS), the Leicester Cough Questionnaire (LCQ), the Hull Airway Reflux Questionnaire (HARQ), Integrative Medicine Outcome Scale (IMOS), Integrative Medicine Patient Satisfaction Scale (IMPSS), a five-level version of the EuroQol Five-dimensional Descriptive System (EQ-5D-5L), the EuroQol visual analog scale (EQ-VAS), yin deficiency score, and serum biomarkers.

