### 2.7. Sample-Size Calculation

This is the first exploratory clinical trial to evaluate the feasibility and preliminary effect of *Maekmundong-tang* administration in patients with nonspecific chronic cough. Therefore, there are no prior literature references for sample size calculation. Referring to a study that recommended a minimum of 12 people per group in a preliminary study in the field of life sciences [28], a total of 24 participants, with 12 participants per group, are needed. Considering a dropout rate of 20%, a total of 30 participants, 15 in each group, were specified as the target sample size.

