### 2.8. Statistical Analysis

The statistical analysis of this clinical trial, in principle, will use full analysis set (FAS) analysis as the main analytical method; if necessary, a per protocol set (PPS) analysis will be additionally conducted. The FAS analysis group is defined as comprising participants with data measured for the outcome measures at least once after being randomly allocated, and all data obtained therefrom are included in the analysis. The PPS analysis comprises only participants included in the FAS analysis who have completed the entire process as specified in the protocol and have no significant violations that affect the trial results. The safety analysis includes all the data obtained from the participants who received the investigational product at least once. 

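### The two 70% rules drop randomised participants from follow-up and mix rule-based removals with true loss in the completion and dropout rates

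*Protocol article*

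**What the plan says.** Two sentences in the protocol article remove participants for what they do after randomisation.

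- Section 2.5 (Interventions): "participants with less than 70% medication compliance at Week 6 will be dropped out".
- Section 2.6.2 (Effectiveness Outcomes): "If less than 70% of the cough diary distributed at each visit has been completed, the participant will be dropped out".

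Section 2.8 makes the FAS the main analysis. It admits anyone with at least one outcome measurement after allocation, and "all data obtained therefrom are included in the analysis". The PPS is an additional analysis, run only if needed.

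Section 2.6.1 states that "the primary purpose of this clinical trial is to evaluate the feasibility of a large-scale herbal-medicine clinical trial for nonspecific chronic cough", and lists eight feasibility outcomes. Four matter most here:

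- Outcome 4, average compliance: "the average percentage of individual participants’ actual use of investigational drugs during the clinical trial period", set against intended use.
- Outcome 5, adherence: "the percentage of participants who take 70% or more of all investigational products compared to the total number of participants enrolled".
- Outcome 7, completion: "the percentage of participants who complete the trial without dropout", with the Week 9 and Week 24 follow-up included and all enrolled as denominator.
- Outcome 8, dropout: those who leave before the end, also out of all enrolled.

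Section 2.9 (Economic Evaluation) collects data on a dropout only until that person's product administration ends. It keeps the Week 24 call for dropouts due to adverse events, intercurrent illness or worsening cough. Low compliance and an incomplete diary are not on that list.

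**The concern.** Low compliance and an incomplete diary are protocol deviations. The plan already has a place for them, the PPS, yet it also ends the person's participation. Two things are at stake.

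The first is data. An analysis set that keeps everything obtained cannot keep what was never collected, and no later analysis plan can recover it. Compliance may be related to response or tolerability, and the arms take different products, so the missing data may be informative and may differ by arm.

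The second is the feasibility reading. Completion and dropout are meant to inform a large trial. If people who would have attended Weeks 9 and 24 are removed by rule, the planner cannot separate retention from adherence.

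**Working it through.** **What each removal costs.** Diaries are kept to Week 9 and collected at Weeks 3, 6 and 9. Compliance is judged at Week 6, when the six weeks of treatment end.

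| Rule and time | Later data not collected |
|---|---|
| Diary, Week 3 | Week 6 (primary CSS and other outcomes), Week 9, Week 24 |
| Diary, Week 6 | Weeks 9 and 24 |
| Medication, Week 6 | Weeks 9 and 24 |
| Diary, Week 9 | Week 24 |

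Only the first row reaches the primary effectiveness outcome. For economic data in that row, section 2.9 still allows collection until the person's product administration ends.

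**Link between outcomes 5 and 7.** Both have all enrolled as denominator. Reading the Week 6 check as cumulative compliance, everyone under 70% is dropped and so cannot be a completer. Completers are therefore a subset of adherers, and completion ≤ adherence even if every low complier would have attended to Week 24. With 30 enrolled, each removal of a would-be completer moves completion down and dropout up by 1/30 = 3.3 points.

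**The plan's own figure.** Section 2.7 says: "Considering a dropout rate of 20%, a total of 30 participants". Check: 24 / (1 − 0.20) = 30, or 12 / 0.80 = 15 per arm. The figure reproduces. The text does not say whether the 20% includes removals under the two rules.

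**Illustration.** The article gives no rates, so every input here is an assumption. Let l be true loss, m the share removed for medication and d the share removed for diary. If the three are independent:

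reported dropout = 1 − (1 − l)(1 − m)(1 − d)

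| l | m = d | Reported dropout | Expected completers of 30 | P(at least 24 complete) |
|---|---|---|---|---|
| 10% | 0 | 10.0% | 27.0 | 0.97 |
| 10% | 10% | 27.1% | 21.9 | 0.26 |
| 10% | 20% | 42.4% | 17.3 | 0.01 |
| 20% | 0 | 20.0% | 24.0 | 0.61 |
| 20% | 10% | 35.2% | 19.4 | 0.06 |
| 20% | 20% | 48.8% | 15.4 | 0.001 |

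The last column is the binomial upper tail with n = 30.

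**Effect of clustering.** Suppose l = 10% and the two 10% lapses fall on exactly the same people. Reported dropout is then 1 − 0.9 × 0.9 = 19.0%, with 24.3 completers and a probability of 0.66. If those people are also the ones who would have left anyway, dropout stays at 10%. For 10% removed by each rule, the range is therefore 10% to 27%.

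**The case against.** The strongest reply is that little of the main comparison is at risk, and much of it stands.

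A reader might infer that the rules delete data. They do not: section 2.8 keeps all data obtained, and nothing says that a dropped participant leaves the FAS. The loss is of data not yet collected.

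A reader might infer that the primary CSS is compromised, or that the arms fall below 12 at Week 6. The medication rule acts at Week 6, when that diary is being handed in. Of the two rules, only the Week 3 diary check comes earlier. At an assumed 8% it leaves 15 × 0.92 = 13.8 per arm. Adding a further 8% for prohibited medicines, which lies outside these rules, leaves 15 × 0.92² = 12.7. The figure of 12 is in any case a rule of thumb for pilot studies, not a power requirement.

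A reader might also infer a bias of known size and direction. The documents support neither. People may stop a product because it fails or because the cough has gone. Section 2.8 plans a mixed repeated-measures model, which uses a person's earlier visits.

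Nor are all the feasibility outcomes affected. Outcomes 1 to 3 concern recruitment. Outcome 5 keeps all enrolled as denominator. Outcomes 4 and 6 are only ambiguous, because the text does not say how dropped participants or their remaining intended days are counted.

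Finally, if the large trial kept the same rules, a dropout rate that includes them would be the relevant planning figure. That is fair, but it helps only that one design. Rates split by reason serve either design.

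**Conclusion.** The point holds in limited form. As written, the two rules end follow-up for randomised participants because of behaviour after randomisation. They cost Weeks 9 and 24 in most cases, and the Week 6 primary CSS only after a Week 3 diary failure. They tie completion to adherence by construction and make the dropout rate a mixture, so two of the eight outcomes that serve the primary purpose cannot be read as retention.

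The 3.3 points per removal and the ordering of outcomes 5 and 7 follow from the definitions, given 30 enrolled and a cumulative compliance check. The rise from 10% to about 27% is an illustration: it rests on assumed rates and independence, and shrinks if lapses cluster. The documents allow no estimate of bias in the arm comparison.

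**What to change.** Replace both sentences with a rule to this effect: compliance or diary completion below 70% is recorded as a protocol deviation and excludes the participant from the PPS only; the participant stays in the FAS and in follow-up, with all remaining assessments to Week 24.

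- **Incomplete diaries.** Where a visit's diary is under 70% complete, set that visit's CSS to missing in the mixed model and keep every other outcome from that visit. Average the recorded days as a sensitivity analysis.
- **Feasibility outcomes.** Report outcomes 7 and 8 as participant withdrawal or loss to follow-up, with reasons, separately from low adherence (outcome 5) and diary compliance (outcome 6).
- **Economic section.** Bring the Week 24 call in section 2.9 into line, so that participants below either threshold are also called.

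Whether the product continues after a diary shortfall is left to the sponsor; this change concerns follow-up and analysis only.

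The cost is protocol wording through the IRB and a few extra visits and Week 24 calls. The target of 30 does not change.

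### Section 2.5 does not separate stopping the product from leaving the study when a listed drug is needed, so Week 6 CSS can be lost for a reason plausibly linked to poor cough response

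*Protocol article*

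**What the plan says.** Section 2.5 (Interventions) has two sentences on concomitant drugs.

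- **Drug required.** Where a participant's circumstances or condition call for it, "the trial should be discontinued if the following medications or treatments are required". The list includes antitussives, expectorants, steroids, antileukotrienes, anticholinergics, LABA, oral antihistamines and traditional Korean treatment for chronic cough. It also includes ACE and DPP-4 inhibitors.
- **Drug received.** For a participant who has had a contraindicated drug that may affect the outcomes, or who cannot go on because of an adverse event or intercurrent disease, "the participants will be dropped from the study at the investigators’ discretion".

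The same section adds a compliance rule: "participants with less than 70% medication compliance at Week 6 will be dropped out".

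Section 2.6.2 states: "The primary effectiveness outcome is the CSS score at Week 6". The analysed value at each visit after baseline is the mean of the diary scores since the previous visit. The dropout trigger for the diary is "If less than 70% of the cough diary distributed at each visit has been completed". At the Week 24 call, "participants will be asked to respond on their cough symptoms during the daytime and nighttime of the previous day".

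Section 2.8 defines the FAS as randomized participants with at least one outcome measurement and says that "all data obtained therefrom are included in the analysis". Effectiveness is analysed with a repeated-measures mixed model, and before-after change within each group with a paired test.

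Section 2.9, on the economic evaluation, collects data on dropouts until their dosing ends. It keeps a consented Week 24 call for those who leave because of an adverse event, intercurrent disease or worsening cough.

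Section 2.6.1 defines the dropout rate (outcome 8) as "the percentage of participants who drop out before the end of the clinical trial to the total number of enrolled participants".

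**The concern.** Stopping a study drug and leaving a study are different events. Section 2.5 treats the need for a listed drug as the second kind, and nothing in the article provides for collecting Week 6 CSS afterwards. A participant who needs an antitussive is plausibly one whose cough has not improved, so follow-up may end for some of the people whose cough scores are most informative.

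Three results are exposed. The Week 6 CSS may be absent, or may average only the early days before the drug. The mixed model keeps any earlier visit value and is valid if missingness depends only on what was observed, but it does not cover worsening after the last recorded visit, which is what might prompt a cough drug. The paired before-after test loses anyone without a Week 6 value, although the Discussion says that before-after effects in both groups are to be observed.

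A feasibility trial should also show how many participants need rescue drugs and whether they can still be followed. Outcomes 7 and 8 as defined cannot show this, because a treatment stop and a dropout become the same event.

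**Working it through.** **1. The plan's own figure.** Section 2.7 needs 24 participants and allows 20% dropout: 24 / (1 − 0.20) = 30, or 12 / 0.80 = 15 per group. This reproduces, and the point does not affect it. The article gives no power, effect size or SD.

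**2. Does another section recover the Week 6 value?**

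- The FAS rule in section 2.8 keeps data that were obtained. It cannot supply data that were not collected.
- Section 2.9 follows dropouts only to the end of dosing, and it is written for the economic evaluation.
- The Week 24 call covers 1 day of CSS, against 21 diary days behind the Week 6 mean.

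**3. How much of the Week 6 value survives.** Inputs: visits at days 21 and 42 (Table 1, nominal), a mean of diary scores since the previous visit, and the 70% diary threshold (section 2.6.2). The Week 6 window is days 22 to 42, or 21 days. Since 0.70 × 21 = 14.7, 15 days are needed. The day of leaving is taken as the last diary day.

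| Last diary day | Days in Week 6 window | Share of window |
|---|---|---|
| 21 or earlier | 0 of 21 | 0% |
| 28 | 7 of 21 | 33% |
| 35 | 14 of 21 | 66.7% |
| 36 | 15 of 21 | 71.4% |

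- Value absent: days 1 to 21, 21/42 = 50% of dosing days.
- Value partial and under 70%: days 22 to 35, 14/42 = 33% of dosing days.

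**4. Effect of the ±4 day visit windows.**

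- Visits at days 17 and 46: absent for 17/46 = 37%. The window has 29 days, of which 21 are needed, so absent or under 70% runs to day 37: 37/46 = 80%.
- Visits at days 25 and 38: absent for 25/38 = 66%. The window has 13 days, of which 10 are needed, so absent or under 70% runs to day 34: 34/38 = 89%.

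**5. Diary days lost overall.** The diary runs to Week 9, which is 63 days. Leaving at Week 3 loses 63 − 21 = 42 (67%). Leaving at day 35 loses 63 − 35 = 28 (44%).

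**6. Link to the compliance rule.** Packs planned: 3 × 42 = 126, and 70% of that is 88.2. Stopping after day 29 gives at most 87 packs (87/126 = 69.0%); after day 30, 90 packs (71.4%). A participant kept in the study after stopping the product on or before day 29 would therefore still be dropped at Week 6 under the compliance rule. The fix must cover this.

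**7. Feasibility rates.** One participant moves outcomes 7 and 8 by 1/30 = 3.3 points. The exact 95% interval for 6/30, the planned 20%, is 7.7% to 38.6%, so the numerical effect on these rates is small against sampling error.

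**The case against.** The strongest case against is that this is a feasibility trial of 30 people with no powered CSS comparison and a 20% dropout allowance already built in. For a drug already received, removal is at the investigator's discretion, so retention is already possible. ACE and DPP-4 inhibitors are on the list and the need for them says little about cough response. The statement on data collection after dropout comes from the economic section, and a condensed article may omit a final visit. Whether to include data after a rescue drug is a legitimate sponsor choice.

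Much of this stands. The discretion is real, though it does not attach to the sentence on drugs that are required. The outcome-related argument is limited to the cough treatments. Section 2.9 is supporting evidence only. But effectiveness is still analysed, and no analysis plan can use data that were never collected. Continued follow-up leaves both choices open, with or without the post-drug data.

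A reader might go further in two ways that the documents do not support.

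- **That 83% of such participants lose the Week 6 value.** The figure 35/42 = 83% is a share of calendar days and merges absent with partial values. The 70% diary rule is a dropout trigger, not an analysis exclusion, so partial averages may still enter the FAS. Only the 50% is strictly absent.
- **That the comparison between arms is biased.** An illustration assumed SD 2, a Week 3 to Week 6 correlation of 0.6, and removal of everyone above one bad-outcome threshold common to both arms. With no true difference it gave no between-arm bias. Each arm's mean looked better by about 0.3 points (10% removed) to 0.5 points (20% removed) under a missing-at-random estimate. None of these inputs is in the article and the mechanism is extreme, so this shows direction only.

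**Conclusion.** The point holds as a design choice that can be improved cheaply; it is not a contradiction in the protocol. Section 2.5 ends participation, and not only dosing, when a listed drug is required, and permits the same when a contraindicated drug has been received. No section shown provides for Week 6 CSS afterwards.

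On nominal visit days the Week 6 value is absent for departures on 50% of dosing days (37% to 66% in the two visit-window cases shown), and partial and under the 70% diary threshold for departures on days 22 to 35.

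This rests on two assumptions: that diary collection ends when the participant leaves, and that needing a cough treatment is plausibly tied to poor response. The number of participants affected is not in the article, so no total loss, CSS shift or between-arm bias is claimed. The change should be made; confidence is medium.

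**What to change.** Amend section 2.5 as follows.

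1. Needing or receiving a listed drug stops the investigational product but does not remove the participant from the study. Discretion for adverse events and intercurrent disease stays as it is.
2. Record the drug and its start date.
3. Continue the diary to Week 9 and the scheduled contacts to Week 24 unless consent is withdrawn.
4. State that such a stop does not trigger the 70% compliance dropout. It still counts against the adherence rate (outcome 5).

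In the analysis, keep all data in the FAS. Add a supportive mixed-model analysis that sets only the CSS values after the drug start to missing. The PPS cannot serve for this, because it removes the whole participant, including valid values from before the drug. Report treatment discontinuation separately from dropout alongside outcomes 7 and 8.

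**Cost.** A wording amendment, one CRF item, and visits already on the schedule for participants who are off treatment. Section 2.11 requires IRB approval of the change and an entry in the registry. The downside is that some CSS values will include rescue-drug effects, which is why the supportive analysis is needed.
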